| Statistical Methods: | Specific Aim 1: To determine feasibility of a randomized trial with REBOOT, we will calculate screening and visit completion rates from the study database, with exact 95% confidence intervals (Cis), overall and by arm. Between-group differences will be assessed using Fisher’s exact and Wilcoxon ranksum tests. We will calculate Kaplan-Meier curves for time to dropout, by group, and test for differences using the log-rank test.  Specific Aim 2: To determine acceptability of REBOOT, we will calculate counseling completion rates from the study database by visit, and tabulate the proportions of active arm participants attending 0-4 counseling sessions. Via CAPI, we will inquire about participant satisfaction with the intervention and belief that it affected their drug use behaviors; responses will be presented as means, medians, or proportions, as appropriate, with 95% Cis.  Specific Aim 3: To evaluate the influence of egocentric social network characteristics on overdose events and naloxone use, we will use GEE Poisson models with robust standard errors to evaluate the association between network size, evaluated at baseline and each return visit, and numbers of experienced and witnessed overdose events in the same period; zero-inflated models will be used if needed. Results from this analysis will inform study design of a full efficacy trial and determine if randomization stratified by network size or targeted sampling strategies to ensure diversity in network size are needed. In addition, we will explore the influence of homophily and assortativity on experienced and witnessed overdose events using similar methods. Newman’s method will be used to calculate assortativity coefficients, a measure of the degree of demographic and risk behavior similarity within participants’ egocentric networks.  **Secondary analyses**: Exploratory analyses include preliminary efficacy estimates of REBOOT in decreasing overdose events (non-fatal or death), decreasing frequency of modifiable overdose / drug-related HIV risk behaviors, and increasing days of abstinence from illicit opioids and in substance abuse treatment.  Treatment effects on frequency of overdose events***.*** To determine if REBOOT, compared to TAU, reduces the risk of overdose among high-risk opioid users who have received take-home naloxone, as measured by the number of overdose events over 16 months. Overdose events will be determined by CAPI every 4 months via time-line follow-back of questions to determine the approximate date of non-fatal overdose that have proven reliable in multiple settings,^1-3^ with fatal episodes identified as above. We expect that repeated overdose events may be reasonably common in a subset of higher risk participants. To take advantage of this information, we will estimate treatment effects using Poisson models for the number of OD events in each reporting period, with robust standard errors to account for within-subject correlation and over-dispersion. |

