### Enrollment Visit

Enrollment tests and procedures will be completed prior to enrollment and receipt of the first counseling session.

On the enrollment visit, participants will be randomized to receive the behavioral intervention (n=40) or TAU (n=20). **Randomization** will be 2:1 using permuted blocks of randomly selected sizes 3 and 6.

Participants will provide a urine toxicology test, and will undergo the baseline CAPI followed by initial counseling for the treatment group and TAU for the reference group. The next visit will be scheduled and participants will be compensated for their time.

Subjects will be compensated $30 for the enrollment visit.

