## Data Analysis

### Primary Analysis

Specific Aim 1: To determine feasibility of a randomized trial with REBOOT, we will calculate screening and visit completion rates from the study database, with exact 95% confidence intervals (Cis), overall and by arm. Between-group differences will be assessed using Fisher’s exact and Wilcoxon ranksum tests. We will calculate Kaplan-Meier curves for time to dropout, by group, and test for differences using the log-rank test.

Specific Aim 2: To determine acceptability of REBOOT, we will calculate counseling completion rates from the study database by visit, and tabulate the proportions of active arm participants attending 0-4 counseling sessions. Via CAPI, we will inquire about participant satisfaction with the intervention and belief that it affected their drug use behaviors; responses will be presented as means, medians, or proportions, as appropriate, with 95% Cis.

Specific Aim 3: To evaluate the influence of egocentric social network characteristics on overdose events and naloxone use, we will use GEE Poisson models with robust standard errors to evaluate the association between network size, evaluated at baseline and each return visit, and numbers of experienced and witnessed overdose events in the same period; zero-inflated models will be used if needed. Results from this analysis will inform study design of a full efficacy trial and determine if randomization stratified by network size or targeted sampling strategies to ensure diversity in network size are needed. In addition, we will explore the influence of homophily and assortativity on experienced and witnessed overdose events using similar methods. Newman’s method will be used to calculate assortativity coefficients, a measure of the degree of demographic and risk behavior similarity within participants’ egocentric networks.

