## Sample Size

**Sample size justification:** The sample will provide typical precision for a pilot study of feasibility and acceptability outcomes. Specifically, we will be able to estimate the mean of continuous outcomes within margins of sampling error (MSEs; half-widths of 95% confidence intervals) of 0.32 standard deviations (SDs) within the active arm, and 0.26 SDs overall; proportions will be estimated within MSEs of 9-16 percentage points in the active arm and 8-13 percentage points overall. For Aim 3 and the exploratory analyses of treatment efficacy, precision and power will be low, as is also typical for a pilot study. In designing the full-scale trial, these exploratory results will be cautiously interpreted in the light of confidence intervals, plausibility, and prior results from the literature.

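### Overdose arm comparison: robust standard errors with 20 controls and no small-sample correction named may give 95% intervals that cover only about 90 to 94.5%

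*Protocol*

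**What the plan says.** The model for overdose counts is in the Protocol Synopsis, Statistical Methods: "Poisson models for the number of OD events in each reporting period, with robust standard errors to account for within-subject correlation and over-dispersion". The outcome is described there "as measured by the number of overdose events over 16 months". The same paragraph anticipates skewed counts: "We expect that repeated overdose events may be reasonably common in a subset of higher risk participants".

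The Enrollment Visit section fixes the arm sizes: "participants will be randomized to receive the behavioral intervention (n=40) or TAU (n=20", in permuted blocks of 3 and 6. The synopsis allows up to 10 additional non-injecting participants, which would bring the control arm to about 23 at most (70/3).

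The Sample Size section gives precision for means and proportions only. It concedes low precision and power for Aim 3 and for efficacy, and says that in designing the full trial "these exploratory results will be cautiously interpreted in the light of confidence intervals, plausibility, and prior results from the literature".

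Nothing in the protocol names a finite-sample correction or a t or z reference for the count models. Nothing excludes them either.

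**The concern.** A robust (sandwich) variance is justified when there are many independent units. Here the unit is the participant, and one arm has 20. The synopsis asks this single device to absorb both within-person correlation and over-dispersion, and expects repeat events to be concentrated in a few people. When a small arm happens to miss its few high-count participants, its mean and its estimated variance are low together, so the interval is shortest when the estimate is furthest off.

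At stake is how the pilot's efficacy estimate is read when the full trial is designed. Of the three guards that the protocol names, the confidence interval is the only one computed from this trial's own data. Low power calls for wide intervals, and a method that shortens them works against the caution promised.

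**Working it through.** **1. The plan's own precision figures.** The protocol states "0.32 standard deviations (SDs) within the active arm, and 0.26 SDs overall". The formula t(0.975, n−1)/√n gives 0.320 at n = 40 and 0.258 at n = 60. The normal version, 1.96/√n, gives 0.310 and 0.253. The stated figures therefore match a t-based calculation: for means the protocol already allows for small samples. It gives no comparable figure for the overdose model.

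**2. The estimator.** With complete periods, an arm-only Poisson model and independence working correlation, the log rate ratio is log(Ȳ₁/Ȳ₀), where Yᵢ is a participant's total count. Its robust variance is the sum over arms of Σ(Yᵢ − Ȳ)² / (ΣYᵢ)².

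**3. Why it is too small.** Within an arm the expected sum of squares is (n − 1)σ², not nσ². The variance is deflated by 19/20 = 0.95 in controls and 39/40 = 0.975 in the active arm. If both arms have the same coefficient of variation, controls carry 2/3 of the variance, so the SE shrinks by √(2/3 × 0.95 + 1/3 × 0.975) = √0.958 = 0.979. Skewness adds the rest: in the over-dispersed simulations the mean robust SE was 0.84 to 0.96 of the true SD.

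**4. Assumptions.** Counts were gamma-Poisson with shape k (variance = mean + mean²/k), mean 0.5, 1, 2 or 4 events per control over 16 months, and rate ratio 1 or 0.5, with 20,000 trials per setting (Monte Carlo error about 0.15 to 0.2 points). For scale, at a mean of 1 the event-free share is (k/(k+1))^k: 44% at k = 2, 58% at k = 0.5 and 67% at k = 0.25.

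**5. Coverage of nominal 95% intervals, 40 v 20.**

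| Over-dispersion | Ordinary robust, z | Mancl-DeRouen, t(58) |
| --- | --- | --- |
| none (Poisson) | 93.9–95.0% | 95.3–96.3% |
| k = 2 | 93.4–94.7% | 94.9–96.2% |
| k = 1 | 92.6–94.1% | 94.1–95.6% |
| k = 0.5 | 91.7–93.3% | 93.2–94.8% |
| k = 0.25 | 89.8–91.8% | 91.7–93.6% |

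At rate ratio 1, the ordinary intervals correspond to rejecting a true null in about 5.7% (k = 2) to 10.2% (k = 0.25) of trials, against a nominal 5%.

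**6. Checks.**
- An overall factor M/(M−1) = 60/59 adds only 0.2 to 0.4 points, because the problem lies in the smaller arm and in the skewness.
- At 400 v 200 (mean 1), coverage returns to 93.6–95.2%, so this is a small-sample effect.
- Fitted GEE Poisson models with four periods, period effects and about 5% dropout per visit gave 91.7–93.0% at k = 0.5 and 89.8% at k = 0.25. Each setting had 600 trials, and five of eight planned settings were completed.
- If 20% of participants contributed nothing (32 v 16), ordinary coverage under over-dispersion would be 88.5–94.6%.

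**7. Price of the correction.** In this model Mancl-DeRouen multiplies each arm's variance by (n/(n−1))²: (20/19)² = 1.108 and (40/39)² = 1.052. With the 2/3 and 1/3 weights, the SE rises by √1.089 = 1.044. The t(58) quantile adds 2.002/1.960 = 1.021. Together, 1.044 × 1.021 = 1.066, or about 7% wider on the log scale.

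**The case against.** The strongest reply is that robust errors are a sound choice for correlated, over-dispersed counts, and that the type of correction and its degrees of freedom are commonly left to a statistical analysis plan, which is not at hand. That stands in part. A reader might infer that the protocol prescribes uncorrected errors with a normal reference; it does not, and if the analysis plan already names a correction, a one-line confirmation settles the matter. The point survives because the method as worded, applied in its ordinary form, gives short intervals in the situation that the protocol itself expects.

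The size also rests on a rate and a dispersion that the protocol does not state. With mild over-dispersion and few events, coverage is 94.3–94.7% (k = 2, mean 0.5), which is of little practical concern. Coverage near 90% needs k = 0.25.

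The consequence is limited. The analysis is exploratory, low power is declared, and no significance threshold or go/no-go rule hangs on the efficacy estimate. Plausibility and prior literature are named beside the intervals.

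Three further readings go beyond the evidence:
- A reader might apply these figures to every GEE Poisson model. Aim 3 regresses counts on network size across all participants, so an argument from 20 controls does not carry over. Abstinence days are bounded within a period. Neither was simulated.
- A reader might treat each dropout as a lost participant. Counts are analyzed by reporting period, so someone who leaves after month 4 or 8 still contributes. Shrinking both arms by the full dropout rate, as in the 32 v 16 check, overstates the effect.
- The clause "zero-inflated models will be used if needed" in Aim 3 might be read as the plan's answer to small samples. It concerns excess zeros and is a separate, minor matter.

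**Conclusion.** The point holds for the arm comparison of overdose counts, in conditional form. With 20 controls and over-dispersed counts, ordinary robust 95% intervals may cover about 90 to 94.5%. The shortfall ranges from negligible under mild over-dispersion to about 5 points at shape 0.25. The direction was the same in every over-dispersed setting at 40 v 20. The magnitude depends on assumed rates (0.5 to 4 events per control) and assumed gamma shapes (2 to 0.25), not on figures in the protocol.

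A reader might conclude that the bias correction settles the matter. It does so only under mild to moderate over-dispersion; at shape 0.25 coverage is still 91.7–93.6%. This is a worthwhile, inexpensive improvement to an exploratory analysis. It does not invalidate the pilot or its feasibility and acceptability aims.

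**What to change.** For the GEE/Poisson arm comparisons:

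- Name a bias-corrected sandwich variance (Mancl-DeRouen or Fay-Graubard) with a t reference on the number of participants minus 2. The simulations used the Mancl-DeRouen form.
- State that this brings coverage close to nominal under mild to moderate over-dispersion but only partly under strong over-dispersion (about 92–94% at shape 0.25).
- Take p-values from a permutation test that respects the 2:1 blocks of 3 and 6. In simulation its level was 3.3–5.5% at a nominal 5%, including at shape 0.25 (1,500 trials per setting, Monte Carlo error about 0.6 points). This corrects the p-value and does not itself repair the interval; the coverage of an interval obtained by inverting the test was not examined.

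The same variance correction is reasonable for the other GEE Poisson models, though its benefit there has not been quantified. Separately, label any zero-inflated model in Aim 3 a sensitivity analysis.

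The cost is a few sentences of analysis wording, a short program and intervals about 7% wider on the log scale. Design, sample size and data collection do not change.

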# INTRODUCTION

## Background

The United States is amidst an opioid crisis, with increasing rates of opioid overdose mortality. While naloxone distribution has demonstrated benefits in reducing opioid overdose mortality, more is needed, in particularly interventions to reduce the risk of overdose occurring in the first place. We developed a brief motivational interviewing intervention, based on the IMB model of behavior change, to address opioid overdose, as well as related HIV/HCV risk behaviors, among persons who already have access to naloxone but remain at high risk for opioid overdose.

## Overall Risk/Benefit Assessment

**Primary Patient Risks:**

We do not anticipate any moderate, severe, or life-threatening adverse events as a result of study participation. If a participant should report or display physical problems (such as hyperventilation, ongoing suicidal ideation, serious emotional distress, or similar problems) study staff will suggest that a call be placed to an appropriate referral agency or crisis hotline. The staff member may also call 911 if deemed necessary. Referral lists for mental health and substance abuse services and crisis hotlines will be available for reference at all times and provided to participants upon request. Study staff will be trained in how to identify, manage, and respond to these events. If needed, study staff will arrange for counselors or medical personnel to provide assistance to those participants that experience any serious effects during the course of the study.

Potential risks from study participation will be explained through the informed consent process. The study will not dispense naloxone to participants. Prior to enrollment, participants will have received naloxone (all community distributed naloxone in San Francisco currently comes from the Drug Overdose Prevention and Education [DOPE] Project); prior receipt of take-home naloxone is one of the study inclusion criteria. Therefore, this behavioral study does not pose any additional risks of pharmacologic agents nor does it raise ethical concerns about withholding this potentially life-saving agent. However, participants are informed of potential risks involved in study participation. Risks include those associated with blood draws, such as bruising around the needle site, the risk of infection at the needle site, and occasional equipment failure in the vacuum tubes. Other potential risks to participants include: unauthorized disclosure of confidential information; discomfort or embarrassment related to specimen collection or questionnaires dealing with personal habits and lifestyle, including drug or alcohol use; possible unwanted encounters with friends or associates in the research setting; and continued drug use, with its attendant risks, including risk of overdose.

**Alternative treatments and procedures in place to mitigate patient risks:** Participants have the alternative of not participating in the study; this decision will in no way influence their treatment by study staff. We will make it clear to all potential participants that they have the alternative of not participating in the study, emphasizing that their decision will in no way influence their treatment by the University, Health Department, or the DOPE Project. We will also offer referrals to inpatient and outpatient substance use treatment facilities and services in San Francisco.

**Benefits:** Potential benefits to participants include: possible cessation or reduction in opioid use and reductions in HIV risk behaviors. Potential benefits to society include determining whether an IMB (Informational-Motivational-Behavior) –based intervention is feasible and acceptable among opioid-dependent, naloxone recipients.

## Compliance

This study will be conducted in compliance with this protocol, Good Clinical Practice (GCP), and all applicable regulatory requirements. There is no DSMB for this study.

# OBJECTIVES

The primary objectives of this study are:

- To determine the feasibility of a randomized trial with REBOOT.
- To determine acceptability of REBOOT.
- To evaluate the influence of egocentric social network characteristics on overdose events and naloxone use.

Exploratory objectives of this study are:

- To determine the preliminary efficacy estimates of REBOOT in decreasing overdose events (non-fatal or death), decreasing frequency of modifiable overdose / drug-related HIV risk behaviors, and increasing days of abstinence from illicit opioids and in substance use treatment.
- To provide a preliminary estimate of the effect of REBOOT, compared to TAU, on overdose risk behaviors, as measured by frequency of using opioids with alcohol, cocaine, or benzodiazepines (the most common modifiable overdose risk behavior), we will use GEE Poisson models with robust standard errors to assess reductions in overdose risks and linear mixed models to assess effects on the RAB scale.
- To provide a preliminary estimate of the effect of REBOOT, compared to TAU, on HIV risk behaviors among high-risk opioid users who have received take-home naloxone, as measured by frequency of using opioids with alcohol, cocaine, or benzodiazepines (the most common modifiable overdose risk behavior); and the HIV Risk Assessment Battery (RAB) drug-related risk scale score over 16 months. We will use GEE Poisson models with robust standard errors to assess reductions in overdose risks and linear mixed models to assess effects on the RAB scale.
- We will use GEE Poisson models with robust standard errors to assess evidence that the intervention increases days of abstinence from illicit opioids and days of drug treatment within each of five 4-month reporting periods.
- We will use GEE Poisson models with robust standard errors to assess evidence that the intervention increases the use of naloxone during overdose events witnessed by participants.
- Given the apparent effectiveness of naloxone alone in reducing overdose mortality, we will analyze all measures to generate descriptive data from the control arm. These include trajectories in self-reported drug use, baseline prevalence and incidence of HIV and HCV, longitudinal records on receipt of naloxone refills, and trends in utilization of EMS after naloxone administration (a potential cost savings of overdose prevention to be explored in future mathematical modeling efforts). Although sample size is small, results will contribute to the limited extant research on this topic and population of opioid users.
- We will also conduct exploratory analyses examining association of incident overdose with well-established, modifiable risk factors, considered as time-dependent covariates. Factors to be considered include: use of selected drugs with opioids; periods of abstinence (self-imposed or structural);^4, 5^ increases in opioid dose,[^6^](#_ENREF_165) in particular after a period of abstinence ≥2 days; and use of opioids from a new source[^3^](#_ENREF_54) or in a new location.[^7^](#_ENREF_162) While these relationships have been assessed in cross-sectional studies, our prospective data will allow us to assess the effects of both recent exposures as well as longer-term exposure patterns.
- Treatment effects and depression will be addressed by examining both modification and mediation of the treatment effect on overdose events by depression, as measured by the Center for Epidemiologic Studies-Depression Scale (CES-D). Effect modification will be examined by comparing treatment effects according to baseline depression score. Mediation will be assessed by examining both steps in the indirect pathway (treatment🡪depression, and depression🡪OD/death, controlling for treatment and potential confounders of the mediator/outcome relationship).

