| Objectives: | The primary objectives of this study are as follows:   1. To determine the feasibility of a randomized trial with REBOOT. 2. To determine acceptability of REBOOT. 3. To evaluate the influence of egocentric social network characteristics on overdose events and naloxone use.   The exploratory objectives of this study are as follows:   1. Preliminary efficacy estimates of REBOOT in decreasing overdose events (non-fatal or death), decreasing frequency of modifiable overdose / drug-related HIV risk behaviors, and increasing days of abstinence from illicit opioids and in substance use treatment. 2. Treatment effects on modifiable overdose risk behaviors. To provide a preliminary estimate of the effect of REBOOT, compared to TAU, on overdose risk behaviors, as measured by frequency of using opioids with alcohol, cocaine, or benzodiazepines (the most common modifiable overdose risk behavior), we will use GEE Poisson models with robust standard errors to assess reductions in overdose risks and linear mixed models to assess effects on the RAB scale. 3. Treatment effects on HIV risk behaviors. To provide a preliminary estimate of the effect of REBOOT, compared to TAU, on HIV risk behaviors among high-risk opioid users who have received take-home naloxone, as measured by frequency of using opioids with alcohol, cocaine, or benzodiazepines (the most common modifiable overdose risk behavior); and the HIV Risk Assessment Battery (RAB) drug-related risk scale score over 16 months. We will use GEE Poisson models with robust standard errors to assess reductions in overdose risks and linear mixed models to assess effects on the RAB scale. 4. Treatment effects on discontinuation of opioid use. We will use GEE Poisson models with robust standard errors to assess evidence that the intervention increases days of abstinence from illicit opioids and days of drug treatment within each of five 4-month reporting periods. 5. Treatment effects on management of witnessed overdose*.* We will use GEE Poisson models with robust standard errors to assess evidence that the intervention increases the use of naloxone during overdose events witnessed by participants. 6. Prospective evaluation of naloxone recipients. Given the apparent effectiveness of naloxone alone in reducing overdose mortality, we will analyze all measures to generate descriptive data from the control arm. These include trajectories in self-reported drug use, baseline prevalence and incidence of HIV and HCV, longitudinal records on receipt of naloxone refills, and trends in utilization of EMS after naloxone administration (a potential cost savings of overdose prevention to be explored in future mathematical modeling efforts). Although sample size is small, results will contribute to the limited extant research on this topic and population of opioid users. 7. Validation of additional modifiable risk factors for overdose. We will also conduct exploratory analyses examining association of incident overdose with well-established, modifiable risk factors, considered as time-dependent covariates. Factors to be considered include: use of selected drugs with opioids; periods of abstinence (self-imposed or structural);^4, 5^ increases in opioid dose,[^6^](#_ENREF_165) in particular after a period of abstinence ≥2 days; and use of opioids from a new source[^3^](#_ENREF_54) or in a new location.[^7^](#_ENREF_162) While these relationships have been assessed in cross-sectional studies, our prospective data will allow us to assess the effects of both recent exposures as well as longer-term exposure patterns. 8. Treatment effects and depression. Treatment effects and depression will be addressed by examining both modification and mediation of the treatment effect on overdose events by depression, as measured by the Center for Epidemiologic Studies-Depression Scale (CES-D). Effect modification will be examined by comparing treatment effects according to baseline depression score. Mediation will be assessed by examining both steps in the indirect pathway (treatment🡪depression, and depression🡪OD/death, controlling for treatment and potential confounders of the mediator/outcome relationship). |

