| Study Design: | We will enroll at least 60 opioid-dependent naloxone recipients with a prior opioid overdose who will be randomized to receive repeated doses of a 45-minute IMB (Informational-Motivational-Behavior) –based counseling session in overdose prevention versus treatment as usual (TAU, defined as information and referrals), and followed over 16 months with 4 counseling sessions at months 0 (enrollment), 4, 8, and 12 for the intervention arm. All participants will complete an opioid urine screen at all visits, a Computer Assisted Personal Interview (CAPI) at enrollment and months 4, 8, 12, and 16, and rapid HIV test (or CD4 & viral load test for positive participants) and rapid HCV test at screening and month 16. |
| Inclusion Criteria: | (1) Age 18-65 years;  (2) Current opioid dependence by SCID;  (3) Urine positive for opioids during screening, excluding prescribed agonist maintenance therapy;  (4) History of prior opioid overdose;  (5) Previously received take-home naloxone;  (6) No serious illnesses likely to progress clinically during trial;  (7) Able and willing to provide informed consent, provide locator information, communicate in English, adhere to visit schedule. |
| Exclusion Criteria: | (1) Suicidal ideation by SCID;  (2) Currently participating in another interventional research study that could possible impact the study’s outcomes of interest;  (3) Any condition that, in the Principal Investigator’s judgment, interferes with safe study participation or adherence to study procedures. |

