# SUBJECT POPULATION

## Number of Subjects and Subject Selection

At least 60 subjects will be enrolled in this study, potentially up to 70, to ensure at least 60 people who inject drugs are included.

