## Pretreatment Assessments

### Screening Visit

Subjects will be screened within 30 days of enrollment to determine eligibility for participation in the study. The screening window can be extended to 42 days in exceptional circumstances. Subjects meeting all of the inclusion criteria and none of the exclusion criteria will return to the clinic within 30 days after screening for enrollment into the study.

Informed consent will be obtained at the beginning of the screening visit. After consent is obtained and eligibility is determined, a locator form is completed and HIPAA form is signed for substance abuse record retrieval and review of medical/criminal records. Screening visit will also include a clinical evaluation (Structured Clinical Interview for DSM-IV [SCID] for opioid dependence and suicidal ideation), blood-borne virus testing (rapid HIV/hepatitis C serology [if no confirmed serostatus] +/- CD4+ t cells & HIV viral load), and a urine toxicology test with expanded opioids.

Subjects will be compensated $10 for the screening visit.

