## Demographic Data and Baseline Characteristics

Demographic and baseline characteristics will be summarized using standard descriptive methods by treatment group and overall.

Demographic data will include sex, self-identified race/ethnicity, and age.

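### Baseline HIV and HCV prevalence is listed as a control-arm estimate, although serostatus is established in all participants before randomization

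*Protocol*

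**What the plan says.** The Protocol states the objective twice, as exploratory objective 6 in the Synopsis and as the sixth exploratory bullet under Objectives. The text reads "we will analyze all measures to generate descriptive data from the control arm. These include trajectories in self-reported drug use, baseline prevalence". The full item in that list is "baseline prevalence and incidence of HIV and HCV". The same list includes drug-use trajectories, naloxone refills and use of emergency services. The stated motive is the apparent effect of naloxone alone on overdose mortality, and the text concedes that the sample is small.

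The timing of testing is given elsewhere. The Study Design entry of the Synopsis has all participants complete an HIV test "and rapid HCV test at screening and month 16". Screening Visit words it as "blood-borne virus testing (rapid HIV/hepatitis C serology [if no confirmed serostatus", so serology is run where status is not already known. Appendix 1 puts both tests at screening and month 16, and randomization at the later enrollment visit. Enrollment Visit gives 40 participants to REBOOT and 20 to treatment as usual. On the total, Number of Subjects and Subject Selection says "At least 60 subjects will be enrolled in this study, potentially up to 70".

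Demographic Data and Baseline Characteristics plans summaries for each arm and for the whole sample. It then adds: "Demographic data will include sex, self-identified race/ethnicity, and age". HIV and HCV status are not mentioned there.

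**The concern.** The objective applies one population to measures of two kinds. Trajectories, incidence, refills and emergency-service use are observed after randomization. In the active arm REBOOT could affect them, so a description of people with naloxone alone has to come from the control arm. Baseline prevalence is fixed before allocation. All participants must already have received take-home naloxone to be eligible, so at baseline the two arms are random subsets of one population. For this quantity the restriction removes no bias and costs precision.

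What is at stake is the usefulness of a descriptive estimate. The objective is justified by its contribution to a thin literature, and for prevalence most of the smallness of the sample would come from the choice of population.

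**Working it through.** **Inputs.** Arm sizes of 40 and 20 are from Enrollment Visit. At a total of 70, 2:1 allocation gives a control arm of 70/3, about 23. The 95% half-width convention is from Sample Size. The Protocol gives no HIV or HCV prevalence, so 10% to 50% is assumed; values from 50% to 90% mirror these.

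**Step 1: reproduce the plan's precision.** Sample Size states 0.32 SD (active arm) and 0.26 SD (overall) for means, and 9–16 and 8–13 percentage points for proportions.

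- Means, t(0.975, n−1)/√n: 2.023/√40 = 0.320 and 2.001/√60 = 0.258. Both agree.
- Proportions, 1.96·√(p(1−p)/n) with p from 0.1 to 0.5: n = 40 gives 9.3–15.5 points (9.6–16.0 with the t quantile); n = 60 gives 7.6–12.6 (7.7–12.9 with t). These agree with the stated ranges to within about half a point.

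The plan states no precision for the control arm.

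**Step 2: baseline prevalence, control arm against all participants.** Exact (Clopper-Pearson) 95% intervals:

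| Assumed prevalence | n = 20 | Half-width | n = 60 | Half-width | Ratio |
|---|---|---|---|---|---|
| 10% | 2/20: 1.2–31.7% | 15.2 | 6/60: 3.8–20.5% | 8.4 | 1.81 |
| 30% | 6/20: 11.9–54.3% | 21.2 | 18/60: 18.8–43.2% | 12.2 | 1.74 |
| 50% | 10/20: 27.2–72.8% | 22.8 | 30/60: 36.8–63.2% | 13.2 | 1.73 |

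In the normal approximation the ratio is √(60/20) = √3 = 1.73 at any prevalence.

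**Step 3: a total of 70.** At 50%, the normal approximation gives 20.4 points with 23 participants and 11.7 with 70, a ratio of 1.74. The conclusion does not depend on the final total.

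**Step 4: compare with the plan's ranges.** At 30% and 50% the control-arm half-width (21.2 and 22.8 points) exceeds the 16 points that is the widest figure in Sample Size. Using all 60 gives 8.4 to 13.2 points, which is essentially the plan's own overall range of 8–13.

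**The case against.** A reader might infer that prevalence will be estimated from the control arm only and that two thirds of the results are discarded. The documents do not support that. Nothing excludes a whole-sample figure, and the data are collected in both arms in any case. The section on baseline characteristics plans whole-sample summaries, and its short list defines demographic data. It does not limit what counts as a baseline characteristic, and serostatus would fit there naturally. This part of the objection stands.

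Control-arm prevalence also has a proper use. Incidence can be estimated only among participants negative at baseline, so control-arm baseline status supplies the at-risk denominator for control-arm incidence. That stands too, and is a reason to keep reporting it.

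A reader might also take it that everyone is tested at screening. Screening Visit makes serology conditional on status not already being confirmed. The safer statement is that status is established in everyone.

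Finally, the choice of tables is ordinary SAP content, and this is one item within one of eight exploratory objectives. That limits the severity. It does not remove the point, because the Protocol does name a population for this estimate, and the baseline section never names HIV or HCV status and so does not clearly replace it.

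**Conclusion.** The point holds as a minor one. Objective 6 places a pre-randomization quantity under a control-arm restriction whose rationale applies only to follow-up measures, and the baseline section does not clearly resolve which population is meant. If the objective is followed as worded, the exact half-width is about 15 to 23 points (n = 20), against about 8 to 13 points with all 60. This rests on assumed prevalences of 10% to 50%, on 2:1 allocation being achieved, and on status being available for every randomized participant. The loss arises only if no whole-sample estimate is reported, which the Protocol leaves unclear. No primary objective, sample-size figure or safety decision is affected.

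**What to change.** In exploratory objective 6 of the Synopsis and the matching bullet under Objectives, state that baseline HIV and HCV prevalence is estimated in all randomized participants with exact 95% confidence intervals. Name HIV and HCV status under Demographic Data and Baseline Characteristics so that the sections agree. Keep the control-arm restriction for trajectories, incidence, naloxone refills and use of emergency services, and report control-arm baseline status as the at-risk denominator for incidence.

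The cost is about one sentence in each place. No new data are needed, and validity is not affected.
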